## Abstract

**Background:**

Fear of cancer recurrence (FCR) is a significant unmet need amongst cancer survivors and is consistently associated with psychological distress and impaired quality of life. Psychological interventions for FCR, such as ConquerFear, have demonstrated efficacy in reducing FCR and improving emotional wellbeing. Unfortunately, there are barriers to the uptake of evidence-based FCR treatments in clinical practice. A stepped-care FCR treatment model may overcome these barriers and has demonstrated potential in people with advanced melanoma. This study aims to evaluate the acceptability, feasibility, and impact of a stepped-care FCR treatment model (*Fear-Less*) in people with other cancer types, who have completed treatment with curative intent.

**Methods:**

Sixty people with early-stage cancer (defined as individuals who have received treatment with curative intent and with no metastatic disease) will be screened for FCR using the Fear of Cancer Recurrence Inventory—Short Form (FCRI-SF). Individuals reporting moderate FCR (FCRI-SF between 13 and 21) will be offered a clinician-guided self-management resource; those reporting high FCR (FCRI-SF ≥ 22) will be offered individual therapy according to the ConquerFear protocol. Participants will complete purpose-built evaluation surveys assessing their FCR screening and intervention experiences. Clinicians will also complete a survey regarding their experiences of the treatment model. *Fear-Less* will be evaluated in terms of (1) acceptability (i.e., patient and clinician experience), (2) feasibility (i.e., referral uptake, treatment adherence, and time taken to screen and deliver interventions), and (3) impact (i.e., pre- to post-intervention FCR changes).

**Discussion:**

The *Fear-Less* stepped-care model is a novel framework for screening FCR and stratifying survivors to the appropriate level of treatment. Our study will provide an indication of whether *Fear-Less* is a feasible and acceptable FCR model of care amongst survivors with early-stage disease and inform further investigations of this model.

**Trial registration:**

Australian New Zealand Clinical Trials Registry (ANZCTR); ACTRN12622000818730.

**Supplementary Information:**

The online version contains supplementary material available at 10.1186/s40814-022-01123-y.

## Background

Fear of cancer recurrence (FCR) describes the fear, worry, or concern cancer will come back or progress [1]. Approximately, 50% of cancer survivors experience moderate-to-high or clinically significant FCR [2, 3]. FCR involves intrusive thoughts, worries, hypervigilance to physical symptoms and either avoidance of, or excessive levels of symptom checking [1]. At clinical levels, FCR is characterized by high levels of persistent worry and hypervigilance or hypersensitivity to bodily symptoms [4] and has been associated with poor day-to-day functioning, reduced quality of life, and increased rates of depression, anxiety, and worry about the future [5]. It is often heightened prior to receiving scan results or attending medical reviews [6]. Untreated FCR has been related to the avoidance of or excessive requests for medical reviews, examinations, or follow-ups, potentially risking adverse health outcomes for survivors and increased health costs to survivors and health services [5, 7–9].

Over the past decade, several psychological interventions have been developed and trialled to address cancer survivors’ FCR [7, 10–17]. These interventions target attitudes, beliefs, and behaviors that may exacerbate or maintain FCR. In addition to significantly reducing levels of FCR, these interventions have led to improvement in emotional wellbeing [10, 11] and quality of life [10]. One intervention is ConquerFear, a five-session manualized treatment [10] developed based on a cognitive processing model of FCR [18]. The intervention targets key processes that contribute to FCR, including worry and excessive threat monitoring, unhelpful beliefs about worry, inappropriate monitoring and screening behaviors, and existential concerns [10]. Compared to a manualized relaxation intervention, ConquerFear was shown to reduce FCR in survivors with early-stage melanoma, breast cancer, or colorectal cancer, with reductions maintained at 6 months. Effects of ConquerFear were shown to be mediated by changes in metacognitions and intrusive thoughts about cancer [19]. ConquerFear was also considered by clinicians to be a sustainable intervention in routine practice [20] and likely cost-effective [21].

Unfortunately, support for managing FCR has been rated the top unmet need for cancer survivors in Australia [22], where barriers remain to the uptake of evidence-based FCR treatment in clinical practice. These barriers include lack of routine screening for FCR (e.g., due to the length of screening measures) [22, 23] and the limited availability of therapists with specialized training to deliver FCR interventions such as ConquerFear [24]. Specific strategies are required to address the systemic barriers to delivery of FCR interventions. The use of the limited available resources is also critical to successful implementation.

A stepped-care approach may provide a solution to these barriers. This approach involves offering treatments of differing intensity tailored to survivors’ level of symptoms that can be identified through routine screening. For mild-to-moderate symptoms, a low-intensity intervention is offered that is accessible and convenient for survivors and requires minimal specialist time to deliver [25, 26]. Examples include brief therapy or a self-help approach. In contrast, a high-intensity intervention, such as traditional individual therapy, is offered for people reporting high levels of symptoms. This approach may be more cost-effective compared to the usual care [27] and may increase appropriate referrals to psychosocial services among cancer patients [28]. Stepped-care models have demonstrated benefits for cancer survivors in the management of insomnia [29] and psychological distress [30].

Similar benefits may accrue for FCR, where a stepped-care approach provides a framework to support FCR screening and appropriate referrals to treatment. This approach has been recommended by Cancer Australia (Australia’s peak national government cancer agency) to manage FCR [31] and could improve accessibility to FCR treatment, given most oncology services have limited clinical resources to support all survivors with heightened FCR [24, 26]. In this model, the more intensive intervention (e.g., ConquerFear) is reserved for people with clinical FCR. This is in keeping with findings that ConquerFear appears more efficacious amongst survivors treated for early-stage cancer who presented with higher baseline FCR scores [19]. Lower intensity interventions can then be offered to survivors experiencing mild-to-moderate levels of FCR. Currently, there is no consensus regarding the type of low-intensity intervention that would be best suited to treat FCR [26]. One option is a guided self-management, which has shown promise for improving FCR. For example, an intervention consisting of a psychoeducational resource accompanied by three 15-min telephone sessions was found to improve FCR among early-stage melanoma survivors [11].

On this basis, our team developed the *Fear-Less* stepped-care model for treating FCR. The lower-intensity step consists of a clinician-guided self-management intervention, which is a purpose-developed resource providing education about FCR and cognitive behavioral strategies to manage FCR. The high-intensity step consists of individual therapy using ConquerFear. This stepped-care model was previously evaluated among survivors with stage IV melanoma treated with immunotherapy and targeted therapies [32]. In this study, survivors were screened for FCR and stratified to the above interventions based on their screening scores. The findings indicated *Fear-Less* was acceptable and feasible to implement for both survivors and clinicians. However, this model has yet to be investigated among early-stage cancer survivors.

### Study aims

Our study aims to extend the *Fear-Less* stepped-care model to people with other types of cancer with early-stage disease. For our study, we have defined “early-stage disease” as survivors who have been treated with curative intent and who do not have metastatic disease. As per the *Fear-Less* model of care, individuals with moderate levels of FCR will be offered a clinician-guided self-management intervention and those with clinical levels of FCR will be offered ConquerFear.

The primary aim of our study is to evaluate the acceptability and feasibility of *Fear-Less* to treat FCR in survivors with early-stage disease. This will include evaluations from the perspectives of both survivors and clinicians. A preliminary evaluation of the impact of the stepped-care program on survivors’ FCR levels will also be conducted.

A second, exploratory aim is to assess a one-item measure of FCR, given a barrier to routine screening is the length of existing measures.

## Methods

### Study design

This study is a single-arm evaluation study which will assess the feasibility, acceptability, and impact of *Fear-Less*. The study adheres to the SPIRIT checklist (see Additional File 1).

### Evaluation of Fear-Less by cancer survivors

#### Participants

The participants will include people with breast, gynecology, or head and neck cancer who have completed treatment with curative intent and do not have metastatic disease.

##### Sample size

Sixty survivors will be recruited. As there is currently no clear consensus regarding appropriate sample size for feasibility studies [33], our target sample size is based on our previous feasibility study for *Fear-Less* amongst survivors with stage IV melanoma [32] and on available funding, resources (e.g., clinician time to deliver the stepped-care interventions), and study duration of 18 months. This sample size is also in line with previous pilot and feasibility trials [34].

##### Inclusion criteria

Survivors must meet the following inclusion criteria to participate in the study:Aged ≥ 18 yearsHave completed treatment with curative intent. Individuals receiving maintenance therapies, such as endocrine therapy, can be included in the study.Able to read and write EnglishAble to give written informed consent

##### Exclusion criteria

Survivors diagnosed with metastatic disease

##### Recruitment and consent

Participants will be recruited from the breast, gynecology, and head and neck clinical services at Peter MacCallum Cancer Centre (Peter Mac), Royal Melbourne Hospital, and Royal Women’s Hospital in Melbourne, Australia. Survivors will complete FCR screening measures (described below) as part of their routine care, for example, during an appointment with their oncologist or by nursing staff completing survivorship care.

Survivors who complete screening and meet the above inclusion criteria will be identified by clinical staff supporting the *Fear-Less* program, such as their oncologist or nurse. These survivors will be provided a leaflet informing them about the *Fear-Less* program and that they will be contacted by a member of the research team. These survivors will then be invited to participate in the evaluation of the stepped-care approach by a member of the research team.

If the survivor is interested in participating, they will be provided with verbal and written information about the project, including the Participant Information and Consent Form (PICF). Consent will be obtained either via an online form or paper form returned using a reply-paid envelope.

#### Study measures

##### Demographics and medical history

Identifying information of the survivor’s name and contact details will be obtained from the medical record and/or consent form only to maintain contact with the patient.

After study consent, survivors’ demographic and clinical characteristics will be collected from their medical record and their treating team. Data collected will include the following:AgeSexCancer typeStage of diseaseTreatment received

##### FCR assessments

FCR screening will be completed using two measures below:Fear of Cancer Recurrence Inventory – Short Form (FCRI-SF): The FCRI-SF [35] is a 9-item instrument assessing the presence, frequency, intensity, and duration of thoughts associated with FCR. Total scores range from 0 to 36 with higher scores indicating higher FCR. The FCRI-SF has shown strong internal consistency (*α* = 0.95), temporal stability (*r* = 0.89), and construct validity.Fear of Cancer Recurrence – One Item Measure (FCR-1): The FCR-1 is a one-item measure assessing the severity of FCR [23, 36]. Survivors are asked to rate their fear of their cancer returning or getting worse on a scale from 0 (no fear) to 10 (worst possible fear). In its initial validation study, the FCR-1 was responsive to changes in FCR over time and showed concurrent, convergent, and discriminant validity [36]. This measure is included to provide further validation and comparison against the FCRI-SF.

##### Survivor experience surveys

Acceptability of the stepped-care program (i.e., whether *Fear-Less* is palatable and satisfactory to survivors [37]) will be assessed via three purpose-designed survivor experience surveys (see Additional File 2). These surveys were adapted from measures developed for our earlier study evaluating *Fear-Less* amongst survivors with stage IV melanoma [32].

The following surveys will be administered to survivors:*The Screening Survivor Experience Survey* will be administered to all participants immediately after providing consent. It is a 10-item measure assessing participants’ prior experience of FCR support (e.g., have they been asked about their FCR levels by a clinician) and includes ratings of the degree to which participants agree or disagree that the screening questionnaires are easy to complete, easy to understand, and acceptable. Open response items ask participants about the importance of screening.*The Self-Management Survivor Experience Survey* will be administered to participants 5 weeks following their receipt of the self-management intervention. It is a 10-item measure assessing the most and least useful aspects of the intervention for each participant, whether they would recommend the intervention and subjective changes in FCR.*The ConquerFear Survivor Experience Survey* will be administered to participants who complete 5 sessions of ConquerFear. It is a 9-item measure assessing the most and least useful aspects of individual therapy for each participant, whether they would recommend individual therapy and subjective changes in FCR.

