##### ConquerFear

ConquerFear consists of five individual sessions that promote value-based goal setting and teach survivor strategies to manage worry and excessive FCR. Each session will be approximately 60 min every 1–2 weeks and will be facilitated by a psychologist face-to-face or via telehealth. Each session is accompanied by home-based practice of skills learned in session and home reading to consolidate skill acquisition.

In Session 1, a FCR-specific assessment will be conducted and the model of FCR on which the treatment program is based will be introduced [18]. Discussion of existential changes brought about by cancer will be introduced as well as value clarification and goal-setting tasks to be completed for homework.

In Session 2, the impact of vulnerability factors (e.g., past traumatic life events) on the interpretation and meaning of FCR will be discussed. The rationale for the practice of Attention Training Technique (ATT) will be discussed, which aims to help patients reduce their rumination and shift their attention more flexibly when thoughts of recurrence occur. Clients will be asked to practice ATT daily throughout the remainder of the intervention.

In Session 3, Detached Mindfulness will be introduced. This is designed to enhance meta-cognition awareness and the ability to become an objective observer of thought content without evaluating or reacting to cognitions.

In Session 4, information about possible symptom recurrence will be provided and guidelines to help participants distinguish those from benign physical complaints. Self-examination practices and medical surveillance will be reviewed. Avoidant or excessive behaviors will be identified, and a behavioral contract to help clients engage in recommended levels of self-examination and follow-up tests will be developed. Beliefs that may underpin FCR will also be explored through Socratic dialog.

In Session 5, the goal-setting task will be reviewed, as well as skills learned during the intervention. A relapse prevention plan will be developed.

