#### Study procedures

Over a 15-week period, eligible survivors who have completed screening will be invited to participate in the *Fear-Less* program. Survivors who provide consent to participate will be stratified into a specific level of care within the stepped-care program based on their screening score on the FCRI-SF [35, 38, 39].

Participants identified as experiencing low FCR (score of <13 on the FCRI-SF) will continue with their usual care with their medical and nursing teams. No further follow-up or additional screening will be undertaken for these participants.

Participants identified as experiencing moderate/subthreshold levels of FCR (score of 13–21 on FCRI-SF) will have a brief discussion with a psychologist on the research team to confirm they are concerned about their level of FCR and would like support for it. Participants who agree to proceed will be offered the clinician-guided self-management intervention.

Participants identified as experiencing high/clinical levels of FCR (score of ≥22 on the FCRI-SF) will have a brief discussion with a psychologist on the research team member to confirm the severity of FCR and whether they would like support for it. Factors that will be assessed during this discussion will include the frequency, emotional impact, functional impact, and avoidance of FCR. Participants whose assessment indicates clinical levels of FCR will be offered ConquerFear. Participants who are considered to have sub-threshold FCR, or who do not wish to take part in the ConquerFear therapy, will be offered the self-management intervention.

Following each intervention, participants will complete the screening questionnaires and a survivor experiences survey relevant to the intervention they received. To minimize missing data, questionnaires and surveys not returned within 2 weeks of receipt will be followed-up by phone and mail/email up to three times, at 2-week intervals. Options for follow-up treatment will also be discussed depending on the survivors’ needs. This may include no further treatment, or referrals to services such as a psychiatrist, additional individual therapy, or peer supports.

The three levels of interventions are summarised in Fig. 1.

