##### Feasibility

The feasibility of the stepped-care approach will be assessed by calculating percentages of survivors who completed screening, percentage of participants who consented to the interventions, percentage adherence to the interventions, and clinician time to deliver screening and interventions. The feasibility criteria (Table 2) are based on previous studies [11, 32, 42].

**Table 2 Tab2:** Feasibility criteria for *Fear-Less*

Outcome	Feasibility criteria
Screening rate	A majority (>60%) of survivors completing screening
Intervention uptake	A majority (>60%) of participants consenting to the intervention
Intervention adherence	• For those receiving the self-management resource, self-reported reading 75% of more of the booklet by two thirds of participants • For those receiving ConquerFear, completion of four or more sessions of the intervention

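### The ConquerFear experience survey is tied to completing all five sessions, so survivor acceptability of the high-intensity step would, read literally, be judged in completers alone

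*Protocol article*

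**What the plan says.** Study aims puts acceptability in the primary aim: "The primary aim of our study is to evaluate the acceptability and feasibility of" the stepped-care model. Under Survivor experience surveys, acceptability to survivors "will be assessed via three purpose-designed survivor experience surveys", and each survey has its own rule on who receives it:

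- The screening survey "will be administered to all participants immediately after providing consent".
- The self-management survey "will be administered to participants 5 weeks following their receipt of the self-management intervention". How much of the booklet was read does not matter.
- The ConquerFear survey "will be administered to participants who complete 5 sessions of ConquerFear".

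The ConquerFear section fixes the length of the course: "ConquerFear consists of five individual sessions". The third rule is therefore a condition of full completion.

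Study procedures states the rule more broadly: "Following each intervention, participants will complete the screening questionnaires and a survivor experiences survey relevant to the intervention they received". It mentions neither completion nor people who stop early.

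Table 2, under Feasibility, sets the adherence criterion for this step: "For those receiving ConquerFear, completion of four or more sessions of the intervention".

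**The concern.** Acceptability is defined in the protocol article as whether survivors find the programme palatable and satisfactory. Stopping therapy early may itself be a sign that it was not. A survey sent on full completion takes its respondents from those who stayed, and so probably from those better disposed to the therapy. It asks which aspects were most and least useful and whether the person would recommend therapy, and people who left could answer these questions most informatively.

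The loss would carry through to the analysis. The qualitative work on acceptability uses free-text answers from the surveys, and the rated items are summarised descriptively. If early stoppers are never sent the survey, their views appear in neither. The Discussion makes later efficacy and cost-effectiveness work depend on a favourable answer here, so a one-sided picture of the high-intensity step would affect that decision.

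**Working it through.** The plan gives no completion rate for ConquerFear and no acceptability figure, so there is nothing of its own to reproduce. The check has two parts.

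**1. The rules side by side**

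| Place | Who is surveyed | Completion condition |
|---|---|---|
| Survivor experience surveys: screening | All participants, after consent | None |
| Survivor experience surveys: self-management | Recipients of the booklet, at 5 weeks | None |
| Survivor experience surveys: ConquerFear | Those with 5 sessions | 5 of 5 sessions |
| Study procedures: both interventions | Participants, for the intervention received | None stated |

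The ConquerFear rule is the most specific statement about that survey and the only one with a completion condition. A coordinator who follows it would not send the survey to a participant who stopped at sessions 1, 2, 3 or 4. One who follows Study procedures might.

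Other data do not fill the gap. Process data record the number of sessions completed, which is a count and not an opinion. Reasons are collected for declining participation, but the article does not mention reasons for stopping therapy. The clinician survey gives staff views. No survey or interview of people who stop ConquerFear is described.

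**2. Possible size (all inputs assumed)**

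Let *c* be the share of starters who complete five sessions, *p*C the proportion of completers who find therapy acceptable, and *p*N the same proportion among non-completers.

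- All-starters figure = *c* × *p*C + (1 − *c*) × *p*N
- Overstatement by a completer-only survey = (1 − *c*) × (*p*C − *p*N)

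With *p*C = 0.90, the completer-only survey reports 90% in every row:

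| *c* | *p*N | All starters | Overstatement |
|---|---|---|---|
| 0.60 | 0.30 | 0.54 + 0.12 = 66% | 0.40 × 0.60 = 24 points |
| 0.60 | 0.70 | 0.54 + 0.28 = 82% | 0.40 × 0.20 = 8 points |
| 0.90 | 0.30 | 0.81 + 0.03 = 84% | 0.10 × 0.60 = 6 points |
| 0.90 | 0.70 | 0.81 + 0.07 = 88% | 0.10 × 0.20 = 2 points |

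If *p*N = *p*C, or if everyone completes, the overstatement is zero.

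With nothing known about non-completers, *p*N can lie anywhere from 0 to 1. The all-starters figure is then bounded by *c* × 0.90 and *c* × 0.90 + (1 − *c*): 54% to 94% at 60% completion, and 81% to 91% at 90% completion. Data collected under the literal rule could not narrow these bounds.

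**The case against.** **The text does not say that only completers are surveyed.** This is true. Study procedures speaks of the intervention received and can be read to cover everyone. It softens the point but does not remove it: the specific rule and the general one differ, and site staff need one instruction.

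**The study is descriptive and drop-out is visible.** Table 2 has no acceptability criterion, so no threshold can be passed wrongly. Table 1 counts those who complete the evaluation, and sessions attended are recorded, so a reader can see how many starters the survey represents. This stands and limits the harm. It does not supply the missing views.

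**People stop for many reasons.** This also stands. That early stoppers are less satisfied is plausible but is not established in the documents, so the direction of the bias is likely and not certain.

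A reader might also draw stronger conclusions that the documents do not support:

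- *That FCRI-SF change scores are completer-only by rule.* The five-session condition attaches to the experience survey alone. Study procedures and Table 1 place the FCRI-SF and FCR-1 after the intervention with no completion condition. Their exact timing for someone who stops early is detail that an article commonly leaves to the full protocol.
- *That four sessions in Table 2 contradicts five in the survey rule.* One is an adherence threshold and the other a survey trigger, so they may differ. The consequence is still odd: a four-session participant counts as adherent but falls outside the survey.
- *That a comparison between the two steps is spoiled.* The study is single-arm, the steps serve different severity bands, and no such comparison is planned.

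**Conclusion.** The concern holds as a conflict over who receives the ConquerFear survey. Read literally, the specific rule restricts the only survivor instrument on the acceptability of the high-intensity step to people who finish it, while the general procedure and the other two surveys carry no such condition. Because the rule governs data collection, a later analysis plan cannot repair it.

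The result is likely to lean towards favourable views, by an amount the documents do not allow anyone to derive. The 2 to 24 points shown above rest wholly on assumed completion of 60–90%, acceptability of 90% in completers and 30–70% in non-completers. The claim is confined to the acceptability survey and does not extend to the FCRI-SF or FCR-1.

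**What to change.** Reconcile the Survivor experience surveys section with Study procedures so that both state one rule: the ConquerFear survey goes to every participant who starts ConquerFear, on completion of session 5 or once discontinuation is recorded. Tying the second trigger to a recorded discontinuation matters, because a person's last attended session is known only in hindsight, and a fixed calendar date could reach someone still in therapy. The reminder schedule already in Study procedures can be used unchanged.

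Report the responses for all starters, with the number of sessions attended and the response rate among those who stopped early. As a clarification only, state that the post-intervention FCRI-SF and FCR-1 are collected at the same contact.

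The change affects data collection and reporting and leaves treatment as it is. It costs a wording edit and a few more surveys. Response among early stoppers will probably be lower, so some uncertainty will remain, but the reported response rate will show how much.
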